## Abstract

Suicidal ideation is prevalent in adolescents and is a marker for subsequent psychiatric vulnerability and symptom severity. Literature shows that blended care (integrating online and offline components in a treatment process) could improve the effectiveness and adherence of interventions targeting suicidal ideation in adolescents, but the evidence is inconclusive. Thus, we will test the effectiveness of a blended intervention to reduce suicidal ideation (primary outcome) in school settings using a single-blind two-armed cluster randomized controlled trial (cRCT). The internet-based component corresponds to the Reframe-IT, a program encompassing eight online sessions based on cognitive-behavioral therapy (CBT) principles. The face-to-face intervention will be delivered through four CBT sessions. Additionally, we will assess the effect of the intervention on the following secondary outcomes: suicidal attempts, depressive symptoms, hopelessness, emotional regulation, and problem-solving skills. Primary and secondary outcomes will be assessed at post-intervention, 3-month, 6-month, and 12-month follow-up. Finally, we will explore the mediation role of cognitive, emotional, and behavioral correlates of suicide on the effect of the intervention. Results will inform whether the intervention can reduce suicide among school adolescents and be implemented on a large scale in Chile.

## 1. Introduction

### 1.1. Background and Rationale

Suicide-related behaviors (SRB) including suicidal ideation (SI) and suicide attempts (SA) are common in adolescents, representing a major health burden [1,2]. The lifetime and 12-month worldwide prevalence of suicidal ideation in this population is 18% and 14.2%, respectively [3]. It is well known that youths are reluctant to seek professional help [4] and that the capability for the early detection of individuals at risk for suicide is low [5]. Accordingly, the literature recommends using evidence-based strategies to actively detect at-risk subjects and provide interventions for reducing suicide risk. Most adolescents receive a formal education [6]. Moreover, school-based interventions can positively impact SRB and overall do not appear to cause harm [7]. Thus, schools are currently considered an accepted context to implement suicide-prevention programs [8,9]. Recently, strategies have called for delivering interventions in face-to-face and digital settings [10]. The evidence shows that combining these two approaches (blended care), could improve their effectiveness [11] and reduce health-related costs; however, further research is needed, mostly in young people from Latin American countries [7].

There has been a rapid growth in the development and usage of internet-based interventions to prevent and treat mental disorders [12]. Digital technologies are currently suitable for improving the appeal, cost, and reach of mental health interventions [13,14]. This is very important for low and middle-income countries [10,15], where the treatment gap of mental disorders is very high [16,17]. Moreover, it is also relevant for improving the treatment for underserved populations [18], such as adolescents [19], who cannot access timely and frequent mental health services [20,21]. Cumulative evidence shows that digital interventions might overcome structural and attitudinal barriers associated with accessing mental health care [22], and that might be effective for reducing SI [23] and repetition of self-harm [24]. Internet interventions based on cognitive-behavioral therapy (CBT) principles have been one of the most studied technology-assisted interventions for mental health, with a substantial part of the interventions targeting depression and anxiety disorders in adults [14]. Some research shows that, when carefully designed, these interventions could improve adherence, satisfaction, and clinical outcomes in adolescents with anxiety and depression [25,26,27,28,29]. However, further research is needed in low- and middle-income countries [30,31,32].

CBT-based interventions seem to be the most promising approach to reduce SRB [33], including SI in adolescents [34,35], but some challenges must be faced to effectively integrate evidence-based programs into real-world adolescent settings [36]. First, online interventions to reduce SRB among adolescents are scant and primarily conducted in developed countries [7]. Two recent reviews [23,37] identified four studies. Van Voorhees et al. [38] observed a reduction in depressive symptoms (DS), yet significant decreases in SI and hopelessness in both control and experimental groups. The protocol by Stallard et al. [39] was reported as a useful and acceptable strategy to manage self-harming thoughts. The community-based pilot RCT by Hill and Pettit [40] yielded reduced perceptions of burdensomeness but not in SI. Finally, Perry et al. [29] observed reduced DS by a cluster randomized controlled trial (cRCT) in educational settings. Although these studies have shown some positive results, only Stallard et al. [39] targeted SRB as the primary outcome.

Second, most of the school-based programs are universal and selective interventions [6]. Most internet-based programs are indirect interventions (targeting depression, anxiety, hopelessness, or burdensomeness). The review by Büscher et al. [41] showed that the only direct intervention targeting suicidal ideation in school students with suicidal ideation is the Reframe-IT, developed by Robinson et al. [42]. This intervention was built following the main principles of CBT, considering the evidence that cognitions are central in the development and maintenance of mental health difficulties and that both emotional and behavioral problems can be resolved by modifying dysfunctional thoughts [43]. The intervention is organized in eight modules to promote the following skills: problem identification, emotional recognition, distress tolerance, behavioral activation, cognitive restructuring, and problem-solving skills. Following international recommendations [44], secondary outcomes such as depression and hopelessness were additionally assessed [45]. The pilot study (pretest/post-test design with an 8-week intervention phase) developed in 11 secondary schools showed that the program was enjoyable, helpful, and acceptable by participants [46] and effective in reducing SI, DS, and hopelessness at post-intervention [47]. The RCT study by Hetrick et al. [48], found improvement in SI levels (intervention group: mean = −61.6, SD 41.6; control group: mean = −47.1, SD 42.3). These differences were not significant, which might be due to the small sample size [49]. Given preliminary results showing that it is a safe online intervention to engage with suicidal young people, further research testing its effectiveness with larger samples is guaranteed [7]. 

Third, prior research has found that direct face-to-face interventions effectively reduced SI in adults [50] and adolescents [51]. The underlying mechanisms explaining this preliminary effect remain uncertain. Very few studies have proposed specific processes [52] beyond anxiety, depression, and hopelessness [23]. The review by Milner et al. [53] found that social support, suicide prevention literacy, and learning alternative coping behaviors could be mechanisms associated with reduced SRB after Brief Contact Interventions (BCIs). This fits with Iyengar et al. [52], who observed that the processes related to reductions in SRB were individually self-driven (behavioral self-regulatory processes) and socially driven (family or social support networks) and that the central components of effective interventions are emotion regulation, problem-solving, and communication skills.

Fourth, digital interventions have shown similar (small and significant) effects to face-to-face programs [37], but the knowledge on processes influencing these effects is limited. Besides the abovementioned processes, human guidance has been suggested as a potential factor in improving internet-based psychological treatment effectiveness [54]. Guided internet-based interventions have been associated with good outcomes and treatment engagement in adolescents and young people, at least for depression and anxiety [31]. Cumulative evidence shows that adherence and effectiveness of these interventions could improve by increasing motivation and interest through strategies that allow users to tailor activities to their natural context and promote ongoing use [55]. Additionally, periodic monitoring of therapeutic activities [56] and reinforcing therapeutic alliance [33] have been reported as relevant factors. This is supported by recent research showing that treatment completion rates could rise when interventions are delivered with real-time guidance in contexts such as schools [26], and that the impact of interventions could be higher if accompanied by a therapist [13]. Thus, it is currently accepted that blended care (the integration of online and offline components in a treatment process) [57] represents a suitable manner to favor the involvement of therapists in internet-based programs, which has been suggested as a potential factor of success for internet-based interventions [14]. 

In summary, there is a recognized need to improve the effectiveness of interventions targeting suicide ideation in adolescents. Recent evidence shows that including face-to-face intervention could improve the effectiveness of these interventions. In this context, we will develop a protocol of a blended intervention combining an internet-based intervention (Reframe-IT) with four face-to-face sessions based on CBT principles. 

### 1.2. Objectives

The main objective of this study is to develop a blended intervention to reduce suicidal ideation and to test its effectiveness among adolescents in secondary schools in Chile at post-intervention and 3-month, 6-month, and 12-month follow-up. Additionally, the study will identify and compare changes in depressive and anxiety symptoms, hopelessness, emotional regulation, and problem-solving skills among adolescents in the intervention group schools and the control group. Finally, we will explore the influence of potential mediators on the observed effects of the integrated blended intervention. 

We hypothesize that the intervention would reduce suicidal ideation among the treatment group compared to the control group at post-intervention. Specifically, we hypothesize that the intervention will lead to the following changes among the treatment group compared to the control group at post-intervention and follow-up: reduced feelings of depression, anxiety, and hopelessness, increased emotional regulation, and problem-solving skills. Finally, we hypothesize that the effect of the integrated blended intervention on suicidal ideation will be mediated by hopelessness, emotional regulation, and problem-solving skills, and partially mediated by CBT skills acquired from the intervention. The results of this study will provide relevant insights to reinforce direct and indicated interventions in educational settings. 

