#### 3.6.1. Primary Outcome

The primary outcome (suicide ideation) will be assessed by the Suicidal Ideation Questionnaire (SIQ) [63], a 15-item self-report measure designed to determine SI in adolescents. Scores are ranked 0–6, with higher scores indicating greater severity of suicidal ideation. The maximum score is 90 and a cut-off score of 31 indicates a clinically meaningful level of suicidal ideation. It has been validated with clinical and non-clinical populations and has shown high levels of internal consistency (α > 0.90) and test–retest reliability (α > 0.90) and high levels of construct and criterion validity [64].

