## 7. Statistical Methods

### 7.1. Statistical Methods for Primary and Secondary Outcomes

We will use descriptive statistics to assess balance across arms at baseline. The primary between-group analysis will be carried out on an intention-to-treat basis for 3-month SIQ scores. We will use linear mixed effects model analysis to compare the intervention and control groups regarding the change in outcome measures from baseline to post-intervention and the follow-up time point. The school is included as a random factor for each outcome measure to account for possible school effect. We will use Fisher’s exact test to compare the frequency of suicide attempt cases between groups. We also will conduct a Complier Average Causal Effect (CACE) analysis to assess the impact of the number of sessions on the primary outcome. All analyses will be performed using STATA 15.01. 

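### The suicidal ideation hypothesis is set at post-intervention, but the primary analysis is set at 3 months, so the two can give opposite verdicts on the trial

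*Protocol article*

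**What the plan says.** The protocol article speaks about timing in several places.

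- **Section 1.2, hypothesis.** For suicidal ideation, the authors expect that "the intervention would reduce suicidal ideation among the treatment group compared to the control group at post-intervention". No later time point is named. The next sentence sets the hypotheses on depression, anxiety, hopelessness, emotional regulation and problem solving at both post-intervention and follow-up.
- **Section 7.1, primary analysis.** "The primary between-group analysis will be carried out on an intention-to-treat basis for 3-month SIQ scores". The following sentence describes a mixed model comparing the arms "regarding the change in outcome measures from baseline to post-intervention and the follow-up time point", with follow-up in the singular and not identified.
- **Section 3.6.1, primary outcome.** "The primary outcome (suicide ideation) will be assessed by the Suicidal Ideation Questionnaire (SIQ"), followed by scoring, cut-off and validity, with no time point.
- **Section 1.2, main objective, and Abstract.** The objective is to test effectiveness "at post-intervention and 3-month, 6-month, and 12-month follow-up". The Abstract lists the same four occasions. Neither ranks them.

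**The concern.** A trial's hypothesis and its primary test should refer to the same quantity. Here one concerns the effect when the intervention ends and the other concerns the effect three months later. These are different clinical claims, and a psychological intervention could plausibly show one without the other.

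If the arms differ in September and no longer differ in December, a report could say that the stated hypothesis was confirmed, and another could say that the primary analysis failed. Each could cite the protocol. A 5% error rate for the main claim holds only if a single test, fixed in advance, carries that claim.

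The gap in Section 3.6.1 adds to this. The complier average causal effect analysis in Section 7.1 is defined on the primary outcome, so it takes over whatever time point the reader supplies.

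**Working it through.** **Step 1: are these two assessments or one?** Section 3.6 lists post-intervention separately from follow-up at 3, 6 and 12 months. Table 1 places baseline in May 2023, the blended intervention from June to September 2023, and outcome assessments in September and December 2023 and later. September fits post-intervention and December fits 3 months. They are distinct measurements.

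**Step 2: is the hypothesis just loosely worded?** Section 1.2 uses post-intervention alone for suicidal ideation and post-intervention plus follow-up for the other outcomes in the next sentence. The text itself separates the two terms, so the first cannot be read as covering the second.

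**Step 3: what does each place imply?**

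| True pattern of effect | Hypothesis in 1.2 | Primary analysis in 7.1 |
|---|---|---|
| Present at post-intervention, gone by 3 months | confirmed | fails |
| Absent at post-intervention, present at 3 months | not confirmed | succeeds |
| Present at both | confirmed | succeeds |
| Absent at both | not confirmed | fails |

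The two agree in the last two rows and disagree in the first two.

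**Step 4: does the sample size settle it?** No. Section 3.8 gives 14 students per school and Section 2.1 gives ten schools and 140 students per arm; 10 × 14 = 140 agrees. But no input is tied to a time point, and no significance level, power or intracluster correlation value is stated. The plan therefore has no error-rate figure of its own to reproduce.

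**Step 5: size of the ambiguity if either time point could decide.** Inputs, all assumed because the document gives none: a two-sided level of 0.05 at each time point (critical value 1.96) and a correlation ρ between the two test statistics from 0 to 0.9.

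- Two-sided, independent tests: 1 − (1 − 0.05)² = 1 − 0.9025 = 0.0975.
- In favour of the intervention only, independent tests: 1 − (1 − 0.025)² = 1 − 0.9506 = 0.0494.
- Correlated tests: the probability that at least one of two standard normal statistics with correlation ρ passes 1.96, from 1,000,000 simulated pairs per value of ρ.

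| ρ | Either direction | In favour of the intervention only |
|---|---|---|
| 0 (formula) | 9.75% | 4.9% |
| 0.3 | 9.5% | 4.8% |
| 0.5 | 9.1% | 4.5% |
| 0.7 | 8.4% | 4.2% |
| 0.8 | 7.8% | 3.9% |
| 0.9 | 7.1% | 3.5% |
| One fixed time point | 5% | 2.5% |

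Section 7.3 rules out interim analyses, so repeated looks during the trial add nothing to these figures.

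**The case against.** The strongest reply is that the protocol has already chosen. Section 7.1, the statistical section, names one primary comparison at 3 months, and nowhere else is a time point called primary. Section 1.2 does not label its post-intervention hypothesis primary or confirmatory, and an expectation about one occasion can stand beside a primary test at another. This reply stands in part: it is wrong to say that the protocol has no rule. It does not remove the conflict, because the only time-specific hypothesis on the primary outcome is still not the one that the primary analysis tests, and no passage explains the difference.

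A reader might go further and infer that success may be claimed at whichever of the four time points turns out significant. The documents do not support that. The objective and the Abstract list the assessment schedule without ranking it, which is ordinary, and no passage says that a result at any of the four counts. An error rate of roughly 9 to 19%, which four interchangeable time points would give under the same assumptions, therefore does not apply here. A multiplicity rule for the remaining time points is commonly left to the statistical analysis plan, which is not shown, so its absence is no fault.

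A reader might also suspect that the registry entry disagrees. The article gives only a registration number and date, so this cannot be judged.

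**Conclusion.** The concern holds as a contradiction between Sections 1.2 and 7.1, left unresolved by Section 3.6.1. An unseen statistical analysis plan could add detail but would not remove it from this document. The main consequence is interpretive: two of the four possible patterns of effect give opposite answers depending on which section is cited.

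The error-rate cost is conditional. Only if either time point could be treated as decisive does the two-sided false-positive rate rise from 5% to about 7 to 10%, and the rate of false claims of benefit from 2.5% to about 3.5 to 4.9%. Both rest on an assumed two-sided level of 0.05 and an assumed correlation between 0 and 0.9. If Section 7.1 is followed strictly, there is no inflation. The matter should be settled before unmasking, because a time point chosen after the results are known would carry little weight.

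**What to change.** Keep the single primary comparison of Section 7.1: SIQ at the 3-month follow-up. Then make these changes:

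- Section 1.2: restate the suicidal ideation hypothesis at 3 months.
- Section 3.6.1: define the primary outcome as the SIQ score at 3 months.
- Section 1.2 objective and Section 7.1: label post-intervention, 6 months and 12 months as secondary time points, and replace the unspecified follow-up time point in the model sentence with the named occasions.
- Registry: check the entry, and align it only if it differs.

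Do this before the masked dataset described in Section 5.1 is unmasked, and date the change. The cost is wording and an amendment notice. No new data are needed. Section 3.8 ties no input to a time point, so nothing in it conflicts with the change, although the document does not show for which time point the sample size was intended.

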#### Eligibility Criteria

Inclusion criteria for the present study are:Secondary students attending grades 9–11.High scores in suicidal ideation, last month (score ≥ 3 in the Columbia Suicide Severity Rating Scale (C-SSRS) [58].Fluent in the Spanish language.

The exclusion criteria are:Suicide attempt(s), last month.Severe depressive symptoms assessed by the PHQ-9 (>19 points).High severity of psychotic symptoms assessed by the Community Assessment of Psychic Experiences-Positive scale (CAPE, P15) [59]; (cut-off = 1.47) [60].

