#### 3.6.2. Secondary Outcomes and Questionnaires

Suicide attempt: two questions assessing whether participants had attempted suicide; if yes, how many attempts?

Anxiety as trait and as state: The State–Trait Anxiety Inventory (STAI-X) [65] is a self-report questionnaire with two scales of 20 items, each assessing state and trait levels of anxiety. Respondents indicate how they generally feel on a 4-point Likert scale from 0 (almost never) to 3 (almost always). The minimum score is 0 and the maximum score is 60 for both scales. Higher scores mean higher trait or state anxiety levels. It has been validated in the Chilean population aged 13–60 years old [66].

Hopelessness: The Beck Hopelessness Scale [67] is a self-report scale with 20 true or false items, nine of which are keyed ‘false’ and 11 are keyed ‘true’. For every statement, each response is assigned a score of 0 or 1 and the total hopelessness score is the sum of the scores on the individual items. The minimum score is 0 and the maximum score is 20. A higher score means higher hopelessness levels.

Social problem solving: The short form of the Social Problem-Solving Inventory Revised (SPSI-R Short Form) [68] is a 25-item self-report instrument measuring two adaptive problem-solving dimensions (positive problem orientation and rational problem solving) and three dysfunctional dimensions (negative problem orientation, impulsivity/carelessness style, and avoidance style). Each item is rated on a 5-point scale ranging from ‘not at all true of me’ (0) to ‘extremely true of me’ (4). The minimum score is 0 and the maximum score is 75. A higher score means a higher social problem-solving capability.

Cognitive-behavioral skills: The Cognitive-Behavioral Therapy Skills Questionnaire (CBTS) [69] is a 16-item scale with two scales measuring two skills: cognitive restructuring (CR) and behavioral activation (BA). Respondents rank each item on a 5-point Likert scale from 1 (I don’t do this) to 5 (I always do this). The minimum score is 15 and the maximum score is 80. A higher score means a higher presence of cognitive-behavioral skills. To assess general CBT skills, we have removed those items that refer exclusively to the practice of CBT sessions (e.g., keep track of the signs and symptoms of my condition); therefore, general CBT skills could be assessed before and after the intervention in both groups. 

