Emotional regulation: The Emotion Regulation Questionnaire for Children and Adolescents (ERQ-CA) [70] is a 10-item self-report scale assessing two ER styles: Cognitive Reappraisal (CR, six items) Expressive Suppression (ES, four items). Items are rated on a 5-point Likert scale ranging from ‘strongly disagree’ (1) to ‘strongly agree’ (5). The minimum score is 10 and the maximum score is 50. A higher score means a higher presence of emotional regulation styles.

Adherence to TAU actions: A research assistant will register all the appointments and attendance of referred students to the primary care clinics. We will assess aspects related to the adherence to the actions included in the TAU.

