**ASSESSMENTS**																				
**Baseline variables** (descriptive features, suicide ideation, suicide attempts, anxiety, hopelessness, social problem and cognitive-behavioral skills, emotional regulation)										X										
**Outcome variables** (suicide ideation, suicide attempts, anxiety, hopelessness, social problem and cognitive-behavioral skills, emotional regulation)														X			X	X	X	X
**DISSE** **MINATION**																	X	X	X	X

X = milestone.

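### Depressive symptoms are a hypothesised secondary outcome, but the plan schedules no measure of them after screening

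*Protocol article*

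**What the plan says.** **Depression as an outcome.** The abstract gives the secondary outcomes as "suicidal attempts, depressive symptoms, hopelessness, emotional regulation, and problem-solving skills" and promises that "Primary and secondary outcomes will be assessed at post-intervention, 3-month, 6-month, and 12-month follow-up". Section 1.2 (Objectives) sets out to "compare changes in depressive and anxiety symptoms, hopelessness, emotional regulation, and problem-solving skills" between the arms. It then predicts, for post-intervention and follow-up, "reduced feelings of depression, anxiety, and hopelessness, increased emotional regulation, and problem-solving skills".

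**Depression as a measurement.** Section 3.6.2 has seven entries: suicide attempt, anxiety (STAI), hopelessness (Beck), social problem solving (SPSI-R Short Form), CBT skills, emotional regulation (ERQ-CA) and adherence to usual care. The outcome row of Table 1 reads "suicide ideation, suicide attempts, anxiety, hopelessness, social problem and cognitive-behavioral skills, emotional regulation". The baseline row lists the same constructs plus descriptive features. The PHQ-9 appears in the exclusion criteria ("Severe depressive symptoms assessed by the PHQ-9 (>19 points") and in Section 2.2, where the screening data serve to establish eligibility.

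**Scoring in Section 3.6.2.** The SPSI-R Short Form has 25 items rated 0 to 4, with two adaptive and three dysfunctional dimensions. Its range is given as "The minimum score is 0 and the maximum score is 75", and higher is read as more capable. The ERQ-CA has six reappraisal and four suppression items and a range of 10 to 50, and "A higher score means a higher presence of emotional regulation styles".

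**The concern.** The plan states a directional hypothesis about depression and then describes data collection that does not include it. If the schedule is followed, an objective has no data, and this cannot be repaired once the assessments have passed. Depression is not a stray mention either. The background in Section 1.1 treats it as one of the outcomes on which the online programme was assessed before, and reports a reduction in the pilot.

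The two scoring entries matter for a further reason. Problem solving and emotional regulation are hypothesised mediators as well as secondary outcomes, and Section 7.2 enters all mediators together. The score that represents each one should therefore be fixed without ambiguity.

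**Working it through.** **1. Depression: stated role against stated collection**

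| Place in the article | Depression present? |
|---|---|
| Abstract, secondary outcomes | Yes |
| 1.2, objective (change compared between arms) | Yes |
| 1.2, directional hypothesis | Yes (reduction) |
| Eligibility Criteria and 2.2, PHQ-9 | Screening only |
| 3.6.2, instruments | No |
| Table 1, baseline row | No |
| Table 1, outcome row | No |

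This is not one construct under two names. The abstract lists depressive symptoms and omits anxiety. Section 3.6.2 and Table 1 list anxiety and omit depressive symptoms. Section 1.2 names both, so anxiety cannot be standing in for depression.

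The screening PHQ-9 does not fill the gap. It gives no post-intervention or follow-up value. It is also not the baseline that Section 3.6 defines, which is one week before the intervention starts. Section 7.1 models change from baseline, so a baseline measure is needed as well as four later ones.

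**2. Score ranges: number of items × lowest and highest item score**

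- SIQ: 15 × 0 to 15 × 6 = 0 to 90, as stated.
- STAI, each scale: 20 × 0 to 20 × 3 = 0 to 60, as stated.
- Hopelessness: 20 × 0 to 20 × 1 = 0 to 20, as stated.
- ERQ-CA: 10 × 1 to 10 × 5 = 10 to 50, as stated.
- SPSI-R: 25 × 0 to 25 × 4 = 0 to 100; stated 0 to 75.

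The figure 75 results from 25 × 3, that is from items scored 0 to 3, which contradicts the 0 to 4 rating in the same entry. Reversing items does not change the range. (The CBT skills entry has a similar slip: 16 × 1 = 16, against a stated minimum of 15.)

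**3. SPSI-R direction**

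The article does not give the number of items per dimension. Assume 25/5 = 5 each.

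- Plain sum, fully adaptive and not at all dysfunctional: 10 × 4 + 15 × 0 = 40.
- Plain sum, the opposite profile: 10 × 0 + 15 × 4 = 60.
- Dysfunctional items reversed (4 minus the answer): 40 + 60 = 100 and 0 + 0 = 0.

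More generally, with *k* adaptive items the plain sums are 4*k* and 4(25 − *k*), so the two profiles rank the wrong way round whenever *k* is 12 or less. At larger *k*, every dysfunctional answer still raises a plain sum. The stated direction therefore requires reversal.

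**4. ERQ-CA total**

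Reappraisal runs from 6 × 1 = 6 to 6 × 5 = 30, and suppression from 4 × 1 = 4 to 4 × 5 = 20. A total of 34 can be 30 + 4 or 14 + 20. The total does not show which style changed.

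**The case against.** **On depression.** An article condenses a fuller protocol, and an analysis plan may exist. That does not dispose of the point. The article describes every other questionnaire outcome with its items, response scale and range, and even lists adherence to usual care. An analysis plan cannot analyse data that the schedule does not collect. If a fuller protocol does schedule the PHQ-9, then Section 3.6.2 and Table 1 are wrong and still need correcting.

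**On scoring.** The opposing case is stronger here, and most of it stands. The SPSI-R entry states a direction that agrees with the hypothesis and calls three dimensions dysfunctional, so the natural reading is that their items are reversed. A reversal rule is detail that a scale manual or analysis plan may hold. No analysis in Section 7 uses the scale maximum, so the 75 alters no test by itself. For the ERQ-CA, the article names the two styles and does not say that their sum is the analysed score. The mediation figure is not shown.

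A reader might infer that the problem-solving and emotional-regulation hypotheses cannot be interpreted, or that their totals would reverse a real effect. The documents do not support that. A reversed sign on the SPSI-R needs an unreversed sum, which the stated direction contradicts. For the ERQ-CA, any dilution or reversal depends on subscale standard deviations, their correlation and a fall in suppression, and the article gives none of these. Nor does it call suppression harmful or say that the programme should lower it.

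**Conclusion.** The depression contradiction holds in full and rests on no assumption beyond the article's own text. As written, there are no depression data at baseline or at any of four later time points, against an explicit objective and directional hypothesis. It should be resolved before baseline assessment.

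The scoring points are corrections of lesser weight. The SPSI-R maximum is wrong on its own inputs (100, not 75), and the reversal that its direction implies is not stated. The 40 against 60 illustration assumes five items per dimension and shows only why the reversal matters. The emotional-regulation hypothesis is not tied to a score, and the only range given is for a total that mixes two styles. No effect size is attached to either point, because the article supplies no inputs for one.

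**What to change.** 1. **Depression.** Add the PHQ-9, which is already administered in Qualtrics for screening, to the baseline, post-intervention, 3-, 6- and 12-month assessments. List it in Section 3.6.2 and in both assessment rows of Table 1, and analyse it with the same mixed model as the other secondary outcomes. The alternative is to remove depression from the abstract, objectives and hypotheses.
2. **SPSI-R.** Correct the maximum to 100 and state that the items of the three dysfunctional dimensions are reversed before summing.
3. **ERQ-CA.** Tie the emotional-regulation hypothesis and mediator to the reappraisal and suppression subscale scores rather than to the total. Which subscale carries the mediation hypothesis is for the investigators to choose and state in advance.

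The cost is nine more items per assessment, or 9 × 5 = 45 per student over the trial, plus an amendment to Table 1 and a few lines of scoring text. No visits or staff are added. Removing depression instead costs only text.
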